#### Power Calculation

On the basis of the aforementioned study design, we assessed the minimum effect size of the team intervention that can be detected with sufficient power (>80%). The percentage reduction in the number of RRT activations in response to adverse events per unit per month (RRT/unit/month) was chosen as the effect size measure because it is the most proximal of the clinical outcomes to the implemented workflow. As shown in Figure 2, our design provides a baseline period of 60 unit months and a team intervention period of 41 unit months. Assuming that the occurrence of RRT events follows a Poisson process, we conducted simulation studies with 10,000 replications to estimate the power curves using the following three scenarios. The first scenario assumes a mean rate of 4.5 RRT/unit/month during the baseline period for all 6 units. The second and third scenarios assume the following heterogeneous mean rates across the 6 units: 3.5 RRT/unit/month for 2 units, 4.5 RRT/unit/month for 2 units, and 5.5 RRT/unit/month for 2 units. In scenario 2, we assume that the team intervention is introduced to the units with lower rates at baseline first and the higher-rate units last, whereas in scenario 3, we assume the opposite. All scenarios use a two-sided α set at .05. Figure 3 shows the power curves for each scenario: scenarios 1, 2, and 3 indicate 80% power to detect a reduction in the RRT event rate of approximately 25%, 18%, and 30%, respectively.

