### Implementation Strategy

The intervention implementation will be split into two stages to assess its impact when offered to the physicians only (stage 1) and later to the entire physician-nurse team (stage 2). In stage 1 (yellow shading in Figure 2), the three alert modes will be delivered only to the physicians for patients across all 6 patient care units, and subsequent workflows will be initiated only by the physician.

In stage 2 (green shading in Figure 2), the alert modes will also be delivered to the nurses on the clinical teams, and either the physician or the nurse on the team can initiate the downstream workflow, thus creating a team approach to identifying and managing clinical deterioration. Nurses are to perform a parallel clinical validation of the alert and contact the physician to conduct the aforementioned risk-of-deterioration huddle. Thus, assessment of the risk and initial steps to manage deterioration can be initiated by either the physician or the nurses in the team intervention model. Stage 2 will be rolled out in a stepwise manner to each of the 6 primary general medicine units.

Rolling out the intervention using a stepwise approach was chosen for pragmatic implementation and evaluation purposes. The physicians care for patients across all 6 patient care units, whereas the nurses are staffed based on individual units. For implementation practicality and patient safety, stage 1 (physician-only intervention) would thus be implemented across all 6 units, whereas the implementation of stage 2 (the addition of nurses) would be staggered by the patient care unit so that the nurses in each unit can be trained in the new workflow together. This implementation strategy also allows us to evaluate the additive impact of delivering AI predictions to the entire physician-nurse team using a stepped wedge design.

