**Figure 2 figure2:**
[figure not shown]
Stepped wedge design for the implementation and evaluation of a clinical deterioration model and workflow. Under *Baseline* column, blue shading includes data from the 10 months prior to the roll-out of the intervention for all 6 participating units (60-unit months for analysis). Under *Month* column, yellow shading represents stage 1 and the physician-only intervention for the physician-nurse team (25-unit months for analysis). Under *Month* column, green shading indicates stage 2 and the intervention for the physician-nurse team (41-unit months for analysis).

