### Analysis

#### Quantitative Analysis

The primary aim is to assess the impact of the physician-only and team interventions on the unit-level clinical outcomes compared with baseline data. The secondary aim is to explore how the intervention is implemented by describing the process outcomes that were developed and launched as part of the intervention-specific workflow. For these process outcomes, the differences between the physician-only and team interventions will be statistically evaluated because baseline data will not be available for these outcomes. Poisson regression will be applied for unit-level count outcomes to determine the differences among the three phases of the study (baseline, physician-only, and team), followed by pairwise comparison. A multilevel, mixed-effects model will be used for patient-level outcomes to include the covariate unit to account for nesting. The level of statistical significance will be set at *P*<.05.

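### The 18% and 30% detectable reductions arise only if units are pooled; under those scenarios pooling biases the rate ratio by roughly 5–9% and raises type I error to about 9–17%

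*Protocol article*

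**What the plan says.** For the counts, Quantitative Analysis states that "Poisson regression will be applied for unit-level count outcomes to determine the differences among the three phases of the study", followed by pairwise comparisons. Its next sentence brings in unit as a covariate, but for patient-level outcomes.

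The Power Calculation section concerns team versus baseline: "our design provides a baseline period of 60 unit months and a team intervention period of 41 unit months". The Figure 2 caption gives every unit the same 10 baseline months. Team months are unequal, because Implementation Strategy says that "Stage 2 will be rolled out in a stepwise manner to each of the 6 primary general medicine units".

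Scenario 1 sets 4.5 RRT events per unit per month everywhere. Scenarios 2 and 3 set 3.5, 4.5 and 5.5, two units each. In scenario 2 "we assume that the team intervention is introduced to the units with lower rates at baseline first and the higher-rate units last"; scenario 3 reverses the order. The section adds that "All scenarios use a two-sided α set at .05" and concludes that "scenarios 1, 2, and 3 indicate 80% power to detect a reduction in the RRT event rate of approximately 25%, 18%, and 30%, respectively". It does not explain why roll-out order alone should move the detectable effect from 18% to 30%.

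**The concern.** If unit is in the model, each unit serves as its own control and roll-out order should hardly affect sensitivity. A swing from 18% to 30% suggests that the simulated test compared the pooled team rate with the pooled baseline rate. Early units carry more weight in the team phase than at baseline. If their rates differ from those of late units, the two pooled rates differ even when the intervention does nothing.

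The 18% would then be a spurious reduction added to the true one, not better power, and the 30% would be a real effect partly masked. If the final analysis also pools, the main contrast for the primary aim carries the same bias. The team-versus-physician-only contrast is exposed to the same mechanism, because early units give few physician-only months; that contrast is not quantified here.

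**Working it through.** **Inputs (protocol article).** 60 baseline unit-months, 10 per unit; 41 team unit-months; unit rates as above; two-sided α of .05; Poisson counts. The split of team months by unit is only in Figure 2, so it is treated as unknown. All non-increasing whole-month splits of 41 over six units, 0 to 11 months each, were enumerated.

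**Pooled test.** Wald test of the log rate ratio, SE = √(1/E0 + 1/E1). E0 = 60 × 4.5 = 270 in every scenario. Let d be the team months of the first two units minus those of the last two. With no effect, E1 = 41 × 4.5 − d = 184.5 − d in scenario 2 and 184.5 + d in scenario 3. The null rate ratio is therefore 1 ∓ d/184.5.

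**Scenario 1 (d plays no part).** At a 25% reduction E1 = 138.4, SE = 0.1045, |ln 0.75|/SE = 2.75 and power is 78.6% (79–80% by simulation). The reduction with 80% power is 25.4%, so the stated 25% is reproduced.

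**Scenarios 2 and 3, pooled.**

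| d | Example split | Null rate ratio, S2 / S3 | Type I error, S2 / S3 | Detectable reduction, S2 / S3 |
|---|---|---|---|---|
| 10 | 10,9,7,6,5,4 | 0.946 / 1.054 | 8.8% / 8.7% | 21.2% / 29.3% |
| 12 | 10,9,8,7,4,3 | 0.935 / 1.065 | 10.6% / 10.3% | 20.2% / 30.0% |
| 14 | 11,10,7,6,4,3 | 0.924 / 1.076 | 12.7% / 12.3% | 19.3% / 30.7% |
| 15 | 11,10,8,6,4,2 | 0.919 / 1.081 | 13.9% / 13.3% | 18.8% / 31.0% |
| 17 | 11,10,9,7,3,1 | 0.908 / 1.092 | 16.6% / 15.7% | 17.9% / 31.7% |

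No split gives 18% and 30% exactly. At d = 14 or 15 both are met to about 1 point.

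*Type I error at d = 15, scenario 2.* E1 = 169.5; SE = √(1/270 + 1/169.5) = 0.0980; shift = ln(0.919)/0.0980 = −0.865. Rejection towards benefit is Φ(−1.96 + 0.865) = 13.7% and towards harm Φ(−1.96 − 0.865) = 0.2%, in total 13.9%. Simulation with 10,000 replications gave 13.5% (scenario 2) and 12.9% (scenario 3).

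*Why 18% and 30% appear.* At d = 15 a true 18% reduction looks like 0.82 × 0.919 = 0.753, and a true 30% reduction looks like 0.70 × 1.081 = 0.757. Both are close to the 25% reduction of scenario 1, shifted by the bias.

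**Unit fixed effects plus phase.** With θ the true rate ratio, λ the unit's rate and t its team months, the information on ln θ is I = Σ 10·λ·tθ/(10 + tθ), and SE = 1/√I. For 11,10,8,6,4,2 in scenario 2 at θ = 0.82, the six terms are 16.6 + 15.8 + 17.8 + 14.8 + 13.6 + 7.7 = 86.4 (from unrounded terms), so SE = 0.1076. Then |ln 0.82|/SE = 1.84 and power is 45%.

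- Detectable reductions for this split: 26.1%, 26.9% and 25.4% in scenarios 1, 2 and 3.
- Over all enumerated splits: 25.5–29.0% in scenario 2 and 25.2–26.0% in scenario 3. Neither 18% nor 30% occurs.
- Simulation over the splits tried: type I error 4.6–5.4%; power for 18% in scenario 2 of 44–49%; power for 30% in scenario 3 of 92–93%.

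**The case against.** **The text does not exclude a unit term.** Quantitative Analysis names a model family and a contrast for the counts, and a condensed article may leave covariates to the full plan. A power simulation may also be simpler than the planned analysis. This stands: a reader might infer that the final analysis certainly omits unit, and the document does not establish that. It does not rescue the power figures. If unit is planned, 18% and 30% do not describe the planned test; if it is not, the test is biased under the plan's own scenarios.

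**A single type I error figure is not supportable.** A reader might settle on about 14%, which belongs to d = 15. The split 11,10,8,6,4,2 leaves the first unit no physician-only month, whereas Implementation Strategy has stage 1 in all six units. If every unit has at least one such month and units cross one at a time, five splits remain. These have d of 10 to 12, type I error of about 9–11% and scenario 2 detectable reductions of 20.2–21.2%. Larger values need units crossing together or a unit without stage 1. The one-unit pilot might explain the latter, but the text does not say so. Hence a range.

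**The bias is conditional.** It needs unit rates that follow roll-out order. The true rates and order are not given, and scenario 1 keeps 5%. A reader might infer that the trial will declare a false benefit or harm; the supported statement is that the chance of doing so is raised under scenarios 2 and 3.

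**Conclusion.** The point stands in this form. The 18% and 30% can be approximated only by pooling units, and they misstate the design's sensitivity. Under scenarios 2 and 3, for d from 10 to 17, the pooled rate ratio is off by roughly 5–9% (10/184.5 to 17/184.5), towards benefit in scenario 2 and harm in scenario 3. Type I error is about 9–17% there, so the stated α of .05 does not hold. With unit in the model the detectable reduction is about 25–27% in all three scenarios for plausible splits (at most 29.0% in scenario 2 under any split). Power for an 18% reduction in scenario 2 is about 45%.

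This rests on Poisson counts without extra variation, whole-month splits and a Wald test. The adjusted type I error near 5% also assumes no calendar trend. All baseline months precede all team months, so a unit term does nothing about trend.

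**What to change.** State in Quantitative Analysis that the Poisson model for unit-level counts contains unit as a fixed effect (six levels) plus phase. Rerun the simulation with that model and the actual Figure 2 split, and replace the 18% and 30% with the results, expected at about 25–27%. Update the scenario 1 figure from the same run; it should change by about a point at most for plausible splits. Report the simulated rejection rate with no effect for each scenario beside the power.

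The roll-out order, chosen on practical grounds, need not change. The cost is one covariate, one rerun of an existing simulation and a less favourable best-case figure. Calendar trend needs separate handling.

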**Figure 3 figure3:**
[figure not shown]
Power curve for simulations with both equal and unequal rapid response team rates across units. RRT: rapid response team.

#### Qualitative Analysis

A SEIPS 2.0 codebook will be created to define each of the concepts and create a shared mental model of the framework for clinical deterioration. Using the documentary data outputs from the process improvement methods to develop the workflow (process maps and pain point analysis) as a starting point, we will develop SEIPS configuration maps that determine important factors for identifying clinical deterioration related to task, person, organization, internal and external environments, and tools and technology—as well as their interactions. The members of the process improvement and evaluation teams will first meet to discuss the SEIPS codebook and then individually produce SEIPS 2.0 configuration maps. These maps will then be consolidated into one agreed configuration map that represents the current state of work for managing clinical deterioration. The SEIPS 2.0 configuration map will then be further refined with data from the interviews. NVivo (QSR International) will be used for data management and analysis. The interview analysis will use a deductive and inductive approach, using deductive codes derived from the SEIPS 2.0 framework and implementation outcomes while searching for emergent themes. The transcripts will be coded by one researcher with a portion of the transcripts coded by a second researcher to check for consistency in identifying themes [19]. The output from the qualitative analysis will be configuration maps before and after the implementation of the model and an assessment of the implementation outcomes, barriers, and facilitators.

#### Mixed Methods Analysis

Data will be mixed during the analysis phase using a mixed methods matrix [20]. Data collected using the aforementioned methods will be mapped to the SEIPS 2.0 framework (eg, data related to *tools and technology* will be gathered in the EHR by extracting number and pattern in the CDI views and in the interviews by asking questions about how the clinicians incorporate the CDI into their workflow and decision-making).

## Results

This study was given a nonresearch determination by the Stanford University Institutional Review Board because the purpose of this study is to develop and evaluate a system to identify and manage clinical deterioration that is specific to the hospital setting. The study began a pilot period of the intervention in one unit in December 2020, and the stepped wedge study began in March 2021.

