**Results:**

A pilot period for the study began in December 2020, and the results are expected in mid-2022.

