### Study Design

To evaluate this complex, multicomponent intervention, we will use a mixed methods approach informed by the SEIPS 2.0 model to achieve our aims of assessing both the clinical outcomes and the processes that produced these outcomes. We found this model to be uniquely equipped to assess the impact of a new technology such as a predictive model because it takes into account both the social and technical aspects of implementation. Using a mixed methods approach will provide complementary data on the effect of the AI-enabled model on the management of clinical deterioration (ie, quantitative data will evaluate the clinical outcomes, and qualitative data will evaluate the processes) [14]. The intervention will be implemented consecutively in the medicine units based on a modified stepped wedge design featuring three stages (Figure 2): the baseline period (stage 0, blue shading) includes the 10-month period before the implementation of the intervention; in stage 1 (yellow shading), the intervention will be launched to all general medicine physicians across the hospital; and in the third and final phase (green shading), the intervention will be launched to the full physician-nurse clinical team in a staggered approach by medical unit. The study began in March 2021 (month 1).

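### Read plainly, the 60-unit-month baseline runs to February 2021 and may include up to 3 unit-months in which the intervention was already being piloted

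*Protocol article*

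**What the plan says.** Three statements in the protocol article bear on this point.

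- **Start of the study.** Study Design says: "The study began in March 2021 (month 1").
- **Baseline.** Study Design defines it as follows: "the baseline period (stage 0, blue shading) includes the 10-month period before the implementation of the intervention". The Figure 2 caption counts it: "blue shading includes data from the 10 months prior to the roll-out of the intervention for all 6 participating units (60-unit months for analysis"). The Power Calculation section uses the same count: "our design provides a baseline period of 60 unit months and a team intervention period of 41 unit months".
- **Pilot.** The Results section says: "The study began a pilot period of the intervention in one unit in December 2020, and the stepped wedge study began in March 2021". The abstract gives the same date: "A pilot period for the study began in December 2020".

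The article gives no calendar dates for the baseline, no end date for the pilot and no name for the pilot unit. It nowhere excludes, reclassifies or adjusts for pilot months. The Quantitative Analysis section compares both the physician-only stage and the team stage with the baseline.

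**The concern.** The baseline is the comparator for both primary contrasts, so it should consist of months without the intervention. The article says that the intervention itself was piloted, not merely training or data capture, and that this began three months before month 1. If those months stay in the comparator and the intervention works, the baseline rate is pulled down and both contrasts with baseline are biased towards no effect. The design has little slack to absorb this, because scenario 1 is planned at about 80% power for a 25% reduction.

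Which months count as baseline also needs to be fixed before the outcome data are examined. A later choice would be open to the charge that it depended on the results.

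**Working it through.** **Calendar.** Month 1 is March 2021 (Study Design). The 10 months before it are May 2020 to February 2021. The pilot began in December 2020 (Results). The overlap is December, January and February: 3 months in 1 unit, or up to 3 of 60 unit-months (5%). *Up to* is the right wording, because no end date or day of start is given for the pilot.

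**Unit-month count.** Baseline: 6 × 10 = 60. Intervention stages: 6 × 11 = 66 = 25 + 41, as in the Figure 2 caption. The counts agree with one another, and a baseline of exactly 60 means that no unit-month has been removed.

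**Inputs for power (Power Calculation, scenario 1).** Baseline rate 4.5 RRT activations per unit per month, 60 baseline and 41 team unit-months, two-sided α = .05, 25% reduction.

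**Formula.** E0 and E1 are the expected event counts in the baseline and team periods, and RR is the apparent rate ratio. Then SE = √(1/E0 + 1/E1), and power = Φ(|ln RR|/SE − 1.96). Each figure was also checked by simulating Poisson counts (200,000 replications, Wald test on the log rate ratio).

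**The plan's own figure.**
- E0 = 60 × 4.5 = 270; E1 = 41 × 4.5 × 0.75 = 138.4.
- SE = √(1/270 + 1/138.4) = 0.1045; |ln 0.75| = 0.2877; ratio 2.752.
- Power is 78.6% by the normal approximation and 79.7% by simulation. The stated 80% at about 25% is reproduced.

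**With k baseline unit-months exposed.** This assumes the full 25% reduction in each exposed month. E0 = 4.5 × (60 − 0.25k), and RR = 0.75/(1 − 0.25k/60). For k = 3, E0 = 4.5 × 59.25 = 266.6 and RR = 0.75/0.9875 = 0.759.

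| Baseline | Apparent RR | Apparent reduction | Power, normal approx. | Power, simulated |
|---|---|---|---|---|
| 60, none exposed | 0.750 | 25.0% | 78.6% | 79.7% |
| 60, 1 exposed | 0.753 | 24.7% | 77.3% | 78.3% |
| 60, 2 exposed | 0.756 | 24.4% | 76.0% | 76.9% |
| 60, 3 exposed | 0.759 | 24.1% | 74.7% | 75.7% |
| 57, the 3 dropped | 0.750 | 25.0% | 77.9% | 78.9% |

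By the normal approximation, the reduction detectable with 80% power is 25.4% as planned, 26.6% with 3 exposed months left in, and 25.6% with them dropped.

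**Sensitivity analysis without those three months in any unit.** Baseline is 60 − 18 = 42 unit-months, so E0 = 42 × 4.5 = 189. SE = √(1/189 + 1/138.4) = 0.1119, and 0.2877/0.1119 = 2.571. Power is about 73% by both methods.

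**The case against.** The strongest reply is that the overlap is inferred. The baseline is defined as preceding implementation or roll-out, and a pilot could be called the first implementation. Anchored there, the baseline would be February to November 2020, with a full 60 unit-months and no exposure. The pilot unit is also not said to be one of the 6, and the Setting section says only that most general medicine patients are in those units. A condensed article may leave exact dates to a fuller document. The bias is also conservative: it cannot create a false benefit, and it does not touch the comparison of the team stage with the physician-only stage.

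Much of this stands, and it limits the size and certainty of the point. It does not remove it. The February to November baseline is stated nowhere and would leave December 2020 to February 2021 in no stage of the study. The article itself fixes the start of month 1, the length of the baseline, the count of 60 and the pilot date, and on their plain reading these overlap. The setting and implementation sections describe the intervention only in the 6 units, which makes it likely, though not certain, that the pilot unit is one of them.

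A reader might infer something stronger, because the Implementation Strategy section says: "The physicians care for patients across all 6 patient care units". If exposure had reached all 6 units for three months (18 of 60 unit-months) at full effect, the apparent reduction would be 18.9% (RR = 0.75/0.925 = 0.811) and power about 51%. The documents do not support this: they place the pilot in one unit and do not say how it was delivered or whether its alerts or workflow reached patients elsewhere. Nor do they support a claim that at least 3 unit-months were exposed. For direct exposure in one unit, 3 is the maximum.

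**Conclusion.** The point holds in a limited form. Taken as written, the plan puts pilot months into the comparator for both primary contrasts. This rests on two inferences: that the baseline ends immediately before March 2021, and that the pilot unit is one of the 6. If both are right, up to 3 of 60 baseline unit-months were directly exposed. If, in addition, the pilot already had the full 25% effect, the rate ratio moves about 1.3% towards no effect (0.759/0.750 = 1.013) and scenario 1 power falls by about 4 points. A shorter pilot or a weaker pilot effect gives less. Severity is minor to moderate: it should be put right because the rule is cheap and belongs in place before analysis, but a bias of this size does not undermine the design.

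**What to change.** 1. State the calendar months of the baseline, which unit hosted the pilot, whether it is one of the 6, and the pilot's start and end dates.
2. If the periods overlap, exclude the pilot unit's exposed months from the baseline or classify them as a separate category. Fix this rule before outcomes are examined.
3. Correct the 60 unit-months in the Figure 2 caption and the Power Calculation section accordingly (57 if all three months are removed).
4. Add a sensitivity analysis that drops December 2020 to February 2021 for all units, to cover possible spread through shared physicians.

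**Cost.** Steps 1 to 3 are a data-selection rule and wording. Removing three unit-months costs under 1 point of power (79.7% to 78.9% simulated). Step 4 leaves 42 baseline unit-months and about 73% power. It also takes the winter months out of the baseline, while the 11 intervention months from March 2021 run to January 2022. It therefore suits a sensitivity analysis better than the primary one.
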